**RESEARCH PLAN**

#### **PI: [name] Study Title:** The Impact of Neighborhoods, Networks, and Depression on Drug Users’ HIV Risk (NND)

**Sponsor’s Protocol # *1071***

**Research Question:**

This study will implement and evaluate a small group, randomized controlled, phase II intervention to reduce depressive symptoms and HIV risk behaviors among inner city drug users. The intervention will include elements of cognitive behavioral therapy (CBT) for depression among impoverished individuals, emphasizing depressive cognitions and behaviors theorized to be associated with depression and with HIV risk behaviors among mildly to moderately depressed drug users. CBT has been found to be a highly successful, cost-effective approach to depression treatment for low-income minorities, and may be an important approach to reducing HIV risk behaviors among depressed inner city drug users.

This study will also longitudinally examine active drug users’ social and environmental pathways to depression and subsequent HIV risk behaviors. Specifically, we will examine hypothesized mediating/moderating effects of neighborhood characteristics, social network factors, and individual level factors on depressive symptoms and HIV risk behaviors.

This study will include multiple phases: (1) Phase 1: Formative Research to gather information from the target population for materials and curriculum for the intervention, (2) Phase 2: Piloting of project protocols and procedures, and (3) Phase 3: Delivery of the full intervention and data collection. At this time, we are only requesting permission for Phase 1: Formative Research and Phase 2: Piloting.

**We are requesting approval for Phase 3: Intervention delivery and data collection.**

**Rationale:**

Inner-city minority populations have high rates of drug use and HIV/STIs. Although there is ample evidence that African Americans’ health disparities are strongly associated with their social, economic, and neighborhood contexts, few studies have documented pathways through which social and neighborhood contextual factors may facilitate or impede infectious disease risk (Diez Roux et al., 2005; Krueger et al., 1990). This study builds on our prior successful HIV prevention intervention research among inner city, African American drug users, and on promising results of our pilot study of a depression treatment intervention (Hawkins et al., 2005). This study extends our extensive previous findings on the major role of social network characteristics in HIV risk, by adding a detailed examination of the role of neighborhood factors in moderating or mediating depression and HIV risk in this population. This study capitalizes on our prior success in recruiting and retaining this hard-to-reach population in research.

Recent research suggests high rates of depression among inner city African American populations, and that depression mediates effects of social contextual factors and HIV risk behaviors. In cross-sectional studies, we found that neighborhood factors were correlated with depression, which in turn was associated with drug use and HIV risk behaviors (Latkin et al., 2005; Latkin et al., in press, Appendix I). In addition to its relationship to HIV risk behaviors, depression is itself an important public health issue. Depression is the third leading cause of loss of quality-adjusted life years in the U.S. (Unutzer et al., 2000), and is associated with high levels of medical expenditures (Simon, 2003). Depression is also a risk factor for medical non-adherence, coronary heart disease (Rugulies, 2002), type II diabetes, and diabetic complications (Eaton, 2002; Higgins et al, 2006), of which this population is at disproportionate risk.

This study will delineate social environmental pathways that lead to depressive symptoms and HIV risk behaviors. Understanding these dynamics is critical for developing sustainable multilevel interventions for HIV prevention. Another aim of this study is to test a behavioral intervention that targets a key pathway to HIV risk behaviors, namely the path between depressive symptoms and HIV risk behaviors. Although it is often acknowledged that social environmental characteristics are important risk factors, few interventions have assessed how social environmental factors may facilitate or impede behavior change. In this study, we expect that individuals who live in more stressful neighborhoods will be more likely to relapse into depression and sexual and drug-related HIV risk behaviors. We also expect that support network factors, such as emotional support, may ameliorate the negative impact of neighborhood stressors. The proposed intervention will target individuals who have mild to moderate levels of depressive symptoms.

**Aims**

The specific aims of the overall study are:

1. Test the efficacy of a cognitive behavioral treatment (CBT) approach to reduce depressive symptoms and HIV risk behaviors among drug users.
2. Examine neighborhood-, social network-, and individual-level mediators and moderators of change in depressive symptoms and drug and sexual HIV risk behaviors over time among intervention and control condition participants.
3. Examine the relationship between neighborhood factors, network characteristics, and individual-level factors on depressive symptoms, drug use, and HIV risk behaviors among all study participants.

**Methods:**

**Study Design and Rationale**

**Phase 3: Full Trial**

**Phase 3** includes a longitudinal social epidemiological study and a randomized controlled phase II clinical trial. The longitudinal study will include assessments at baseline, 6m, 12m follow-up. A subset of the longitudinal study sample will be eligible for the RCT which will consist of 2 arms- intervention and control condition.

**Population:**

**Phase 3: Full Trial**

Approximately 500 crack smokers and 500 injectors will be recruited to participate in the longitudinal component of the study (i.e. baseline and follow-up assessments) Of these, approximately 250 crack smokers and 250 injectors with CES-D scores ≥16 will be randomly assigned to either the depression intervention or control condition.

**Statistical Analysis Plan**

**Phase 3: Full Trial**

Several data analysis methods will be used to examine the longitudinal data as well as evaluate the intervention by comparing the 2 treatment arms.

For all estimates of the prevalence of behaviors, outcomes (e.g., depressive symptoms) in this population, we will weight the observations to reflect the oversampling of individuals with higher levels of depression for follow-up assessments. For all other models, we will not weight the observations. In testing hypotheses, it is often necessary to adjust for potentially influential covariates that are not the primary focus of the hypothesis. In the case of independent variables that are continuous, we will use multiple linear regression or other modeling strategies to account for covariates. When the dependent variable is dichotomous or polytomous, we will use log-linear or logistic models, or similar techniques. Model fitting will be accomplished using techniques such as hierarchical stepwise regression and the score test to compare nested models. Due to the nature of sampling and study design, there may be some clustering of data, such as clustering by geographic area or intervention group, which can bias estimates. When needed, statistical techniques that allow for analysis of clustered data we will use, such as Generalized Estimating Equations (GEE) to analyze data clustered by neighborhoods (Liang et al., 1996) and Hierarchical Linear Models (HLM) (Byrk et al., 1992) to provide additional information about factors attributable to the level 2 variance. In addition to handling clustering, HLM will be used to conduct analysis with consideration of both individual and contextual factors. Analysis of data at different levels presents methodological challenges, namely correlations of residual errors among observations nested in higher-level units. Such built-in correlation of errors in hierarchical models violates the assumption of independent errors in conventional statistical procedures. However, multilevel or hierarchical analysis takes into account the built-in correlation of errors in multilevel data (Peacher et al., 2004). It has been applied to contraceptive studies (Krull et al., 2001;1999), needle sharing (Korff et al., 1992), and condom use (Morisky et al., 2002).

For several of our hypotheses, often the individual measures of risk behaviors do not meet linearity assumptions. Use of a composite risk score of risk behavior as the outcome measure has been strongly encouraged by Aral and Peterman (1996), and often addresses the problem of non-linearity. Additionally, transformations, such as taking the square root or natural log, can improve the distribution of the risk behavior variables so that their residuals are distributed approximately normally. As the present study is longitudinal in design and different risk behaviors can change in opposite directions, an indicator of the participant’s overall net risk change is most informative. To test separate hypotheses regarding inject and sexual risk behavior, separate composite scores for each will be generated. The composite score for injection risk behavior will include frequency of sharing needles (without cleaning), cookers, rinse water, and cotton. The composite score for sex risk behavior will include frequency of vaginal sex without a condom, anal sex without a condom, exchanging sex for money or drugs, sex with HIV+, sex with IDU, and number of partners in the past 3 months

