# Power calculations

# The main outcomes of interest are changes in injection and sexual risk behavior and in level of depressive symptoms. A sample size of 200 in each group is assumed for comparisons of sex risk behaviors and depressive symptoms after two years of follow-up with a 10% attrition rate per year. Only half of the sample will be IDUs, and it is assumed that there will be a sample size of 100 per group with the same attrition rates. There will be approximately 50 cohorts (25 intervention cohorts and 25 control cohorts) of with approximately 8 members with complete data at the end of the two years. The power was calculated for an assessment of intervention effectiveness at the end of the study, when sample sizes will be smallest and thus underestimates likely power for comparisons made earlier in the study. Power calculations were done using NCSS/PASS software. Based on the SHIELD study (IRB# H.30.00.07.17.A), we would expect an average CES-D score of 26.7 and variance of 8.3, given the selection methods proposed in the present study. We estimated power with a 2-sided test, setting the alpha at 0.05, with a total sample size of 400. We expect a small amount of correlation due to intervention group (0.02 in the SHIELD Study). A difference between the two groups post intervention on mean CES-D score of 2.0 provides sufficient statistical power.

|  | **Intercluster correlation** | | |
| --- | --- | --- | --- |
| **Difference in mean CES-D score** | 0.00 | 0.02 | 0.05 |
|  | **Power** | | |
| 2.0 | 0.92 | 0.88 | 0.83 |
| 3.0 | 0.99 | 0.99 | 0.99 |
| 4.0 | 1.00 | 1.00 | 1.00 |

Prior studies suggest a larger effect size for intervention effects on injection as compared to sexual risk behaviors. Consequently, despite the smaller sample size for injection risk comparisons, we expect analyses of the two outcomes to have similar statistical power. We based estimates of expected reduction in risk behaviors on the SHIELD study, creating composite scores for injection risk behavior (needle and cooker sharing and frequency of injecting) and sexual risk behavior (9 risk behaviors). The injection risk score had a mean of 11.6 (SD=4.5). The sex risk composite score had a mean of 1.9 (SD=1.8).

|  | Intercluster correlation | | |  | Intercluster correlation | | |
| --- | --- | --- | --- | --- | --- | --- | --- |
| Diff. in mean injection risk score | 0.00 | 0.02 | 0.05 | Diff. in mean sex risk score | 0.00 | 0.02 | 0.05 |

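### The arm comparison accounts for session-group clustering only conditionally, allows stepwise choice of covariates, and does not name the baseline value as a covariate

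*Protocol*

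**What the plan says.** The Statistical Analysis Plan section for the full trial opens by saying that its methods serve both the longitudinal data and the evaluation of the intervention between the two arms. Three features bear on the arm comparison.

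- **Model choice.** "Model fitting will be accomplished using techniques such as hierarchical stepwise regression and the score test to compare nested models". The randomised comparison is not exempted. Covariate adjustment is allowed, but no covariate is named.
- **Clustering.** The section recognises that clustering by intervention group can distort estimates, and then says "When needed, statistical techniques that allow for analysis of clustered data we will use". GEE is tied to neighbourhoods. HLM is offered in general terms and is not required for the arm comparison.
- **Outcome.** The power section says "The main outcomes of interest are changes in injection and sexual risk behavior and in level of depressive symptoms". The paragraph on composite scores also favours a net change in risk. The power calculation itself compares post-intervention means.

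The power section treats group clustering as present: "We expect a small amount of correlation due to intervention group (0.02 in the SHIELD Study". It also gives the structure: "There will be approximately 50 cohorts (25 intervention cohorts and 25 control cohorts) of with approximately 8 members with complete data".

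**The concern.** Group sessions create clusters by design. The plan expects the resulting correlation and carries it through its power tables, but its analysis text does not commit to modelling it. If an analyst judges that clustering need not be handled, the standard error of the arm effect is too small, the interval too narrow and the test too liberal. The documents give no rule for making that judgement.

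Two further choices weaken the primary comparison. Covariates for a randomised contrast may be selected on the outcome data, so the Aim 1 estimate is not fixed in advance. And the outcomes are framed as changes. A change score is less precise than adjustment for baseline and, at low baseline to follow-up correlation, less precise than ignoring baseline altogether. This matters because the power for 2.0 CES-D points is lower than the protocol states.

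**Working it through.** **Inputs from the power section.** Two-sided alpha 0.05; 200 per arm for CES-D and sex risk; 100 per arm for injection risk; 25 cohorts per arm of about 8; ICC 0.02 expected, 0.05 also tabulated; CES-D difference 2.0. The text calls 8.3 a variance. I read it as an SD, because a variance of 8.3 gives power of 1.00 in every cell. The correlation r between baseline and follow-up CES-D is not given; I assume 0.3, 0.5 and 0.7.

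**The plan's own figure.** Stated power for 2.0 points is 0.92 / 0.88 / 0.83 at ICC 0.00 / 0.02 / 0.05. With SD 8.3, 200 per arm and a normal approximation I get 0.67 / 0.62 / 0.54. The stated row matches 400 per arm (0.93 / 0.89 / 0.83). That is a separate defect of the table. Here it shows only that precision is short.

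**Type I error if clustering is ignored.** Design effect DE = 1 + (m − 1) × ICC. True error of a nominal 5% test = 2 × [1 − Φ(1.96/√DE)]. For injection risk, m = 100/25 = 4.

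| Outcome | m | ICC | DE | 1.96/√DE | Type I error |
|---|---|---|---|---|---|
| CES-D, sex risk | 8 | 0.02 | 1.14 | 1.836 | 6.6% |
| CES-D, sex risk | 8 | 0.05 | 1.35 | 1.687 | 9.2% |
| Injection risk | 4 | 0.02 | 1.06 | 1.904 | 5.7% |
| Injection risk | 4 | 0.05 | 1.15 | 1.828 | 6.8% |

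At m = 8 the intervals would be too narrow by 1 − 1/√1.14 = 6% and 1 − 1/√1.35 = 14%.

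If only the intervention arm were clustered, the average design effect at m = 8 would be (1.14 + 1)/2 = 1.07 or (1.35 + 1)/2 = 1.175. The errors would then be 5.8% and 7.1%.

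**Stepwise selection.** A null simulation used 400 participants in 50 clusters of 8, 20 candidate covariates, forward selection and 3,000 runs (Monte Carlo SE about 0.004).

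- At ICC 0, three stepwise variants gave 0.051 to 0.053, so no visible inflation.
- With clustering present but ignored, stepwise with the arm forced in gave 0.065 (ICC 0.02) and 0.099 (ICC 0.05), against 0.055 and 0.091 without selection. These runs mix two problems, and gaps of about one point do not establish a stepwise effect.
- A t test on cluster means stayed at 0.042 to 0.053.

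**Power by use of baseline.** SE = SD × k × √(2 × DE/200), where k is 1 for post-only, √(2(1 − r)) for a change score and √(1 − r²) for baseline adjustment. DE = 1.14. Power comes from the noncentral t with 2 × 25 − 2 = 48 df (critical value 2.011). Post-only: SE = 8.3 × √(2.28/200) = 0.886, 2.0/0.886 = 2.257, power 0.60.

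| r | Change score: SE, power | Baseline-adjusted: SE, power |
|---|---|---|
| 0.3 | 1.049, 0.46 | 0.845, 0.64 |
| 0.5 | 0.886, 0.60 | 0.767, 0.72 |
| 0.7 | 0.686, 0.81 | 0.633, 0.87 |

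The variance ratio of adjusted to change score is (1 − r²)/(2(1 − r)) = (1 + r)/2, or 0.65 / 0.75 / 0.85. On this basis baseline adjustment reaches 0.80 at r of about 0.61 and the stated 0.88 at about 0.71. The calculation assumes that adjustment leaves the ICC unchanged.

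**The case against.** Several arguments on the other side are fair.

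- **Stepwise fitting and type I error.** A reader might infer that stepwise fitting inflates type I error. The documents do not say that models are chosen by looking at the treatment effect, the sentence offers stepwise regression only as an example, and the simulation at ICC 0 shows no visible inflation. What stands is the analyst freedom.
- **Use of baseline.** A reader might infer that the plan makes no use of baseline. It does: a change score contains the baseline value, and covariate adjustment is permitted. Nor is a change-score model actually specified. What stands is that no passage names the baseline value as a covariate in the arm comparison.
- **Recovered power.** A reader might infer that baseline adjustment would restore the stated power. That needs a correlation of about 0.7, which the documents do not give. Against a post-only comparison the gain at r = 0.3 is small (0.60 to 0.64).
- **A test for clustering.** A reader might take the conditional wording to mean a significance pretest. No such test is described, so how often clustering would be dropped cannot be stated.
- **Cluster size.** One year of 10% attrition from 250 per arm would give 225 per arm, or 9 per cohort, and errors of 6.9% and 9.8%. The power section states 8 and 200, so I use those.
- **Upper bounds.** The control arm has one session of about 90 minutes, so its clustering may be weaker. Individuals are randomised from those attending on the same day, so shared batch effects largely cancel between arms. Both points stand, although the power section counts control cohorts too.
- **Detail for a separate analysis plan.** Full model specification may sit in a document not shown. But the conditional clustering rule and the stepwise sentence are choices this protocol states, not omissions.

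**Conclusion.** The point holds in a limited form. The protocol expects clustering by intervention group and recognises the harm it can do, yet makes its handling conditional for the randomised comparison. If clustering is dropped, type I error is at most about 6.6% at the expected ICC and 9.2% at ICC 0.05, with smaller figures for injection risk. That is modest at the expected ICC and more serious at the upper tabulated value. The figures rest on equal clustering in both arms and the stated cohort sizes.

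The objection to stepwise selection concerns pre-specification, not error inflation. The case for naming the baseline covariate is one of efficiency: over the assumed correlations it is at least as precise as either alternative, but it only partly offsets the power shortfall unless the correlation is near 0.7. The change is worth making because it is nearly free, though the conduct of the trial does not depend on it.

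**What to change.** For Aim 1, state one fixed model per main outcome:

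- Regress the follow-up value on arm, the baseline value of that outcome and injector/crack group.
- Always include a random effect for the intervention or control session group (or use GEE with a small-sample correction), with group-level degrees of freedom.
- Use no stepwise selection.

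Keep stepwise fitting and the neighbourhood models for Aims 2 and 3.

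The cost is analysis wording; the baseline survey already collects what is needed. If the true ICC is zero, intervals widen slightly: with 48 group-level df the critical value is 2.011 instead of 1.966 with 398 df, about 2%. The power table needs its own correction, since this change does not repair it.

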# Power calculations

# The main outcomes of interest are changes in injection and sexual risk behavior and in level of depressive symptoms. A sample size of 200 in each group is assumed for comparisons of sex risk behaviors and depressive symptoms after two years of follow-up with a 10% attrition rate per year. Only half of the sample will be IDUs, and it is assumed that there will be a sample size of 100 per group with the same attrition rates. There will be approximately 50 cohorts (25 intervention cohorts and 25 control cohorts) of with approximately 8 members with complete data at the end of the two years. The power was calculated for an assessment of intervention effectiveness at the end of the study, when sample sizes will be smallest and thus underestimates likely power for comparisons made earlier in the study. Power calculations were done using NCSS/PASS software. Based on the SHIELD study (IRB# H.30.00.07.17.A), we would expect an average CES-D score of 26.7 and variance of 8.3, given the selection methods proposed in the present study. We estimated power with a 2-sided test, setting the alpha at 0.05, with a total sample size of 400. We expect a small amount of correlation due to intervention group (0.02 in the SHIELD Study). A difference between the two groups post intervention on mean CES-D score of 2.0 provides sufficient statistical power.

|  | **Intercluster correlation** | | |
| --- | --- | --- | --- |
| **Difference in mean CES-D score** | 0.00 | 0.02 | 0.05 |
|  | **Power** | | |
| 2.0 | 0.92 | 0.88 | 0.83 |
| 3.0 | 0.99 | 0.99 | 0.99 |
| 4.0 | 1.00 | 1.00 | 1.00 |

Prior studies suggest a larger effect size for intervention effects on injection as compared to sexual risk behaviors. Consequently, despite the smaller sample size for injection risk comparisons, we expect analyses of the two outcomes to have similar statistical power. We based estimates of expected reduction in risk behaviors on the SHIELD study, creating composite scores for injection risk behavior (needle and cooker sharing and frequency of injecting) and sexual risk behavior (9 risk behaviors). The injection risk score had a mean of 11.6 (SD=4.5). The sex risk composite score had a mean of 1.9 (SD=1.8).

|  | Intercluster correlation | | |  | Intercluster correlation | | |
| --- | --- | --- | --- | --- | --- | --- | --- |
| Diff. in mean injection risk score | 0.00 | 0.02 | 0.05 | Diff. in mean sex risk score | 0.00 | 0.02 | 0.05 |
|  | **Power** | | |  | **Power** | | |
| 1.0 | 0.60 | 0.57 | 0.54 | 0.25 | 0.54 | 0.49 | 0.43 |
| 1.5 | 0.91 | 0.89 | 0.87 | 0.50 | 0.98 | 0.97 | 0.94 |
| 2.0 | 0.99 | 0.99 | 0.98 | 0.75 | 1.00 | 1.00 | 1.00 |
| 2.5 | 1.00 | 1.00 | 1.00 | 1.00 | 1.00 | 1.00 | 1.00 |

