***Follow-up Visits***

Follow-up surveys will be conducted at 6 and 12 months after the intervention. All participants who meet the longitudinal study eligibility criteria will be invited to participate in the follow-up visits. Participants will be informed of these follow-up visits during the informed consent process at the baseline visit. Approximately 1 month before their follow-up date, staff will contact clients through phone calls and letters to remind them of upcoming follow-up assessments. A copy of the reminder letter for each follow-up period is included.

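### The power section sizes the trial for a comparison after two years of follow-up, but the last scheduled assessment is at 12 months

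*Protocol*

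**What the plan says.** The Power calculations section of the protocol gives the time point and the loss to follow-up together: sex risk and "depressive symptoms after two years of follow-up with a 10% attrition rate per year". The sizes for that point are as follows.

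- For sex risk and CES-D: "A sample size of 200 in each group is assumed for comparisons of sex risk behaviors and depressive symptoms".
- For injection risk: "it is assumed that there will be a sample size of 100 per group with the same attrition rates".
- For the 50 cohorts, 25 in each condition: "with approximately 8 members with complete data at the end of the two years".

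The section then ties the power figures to the final time point: "The power was calculated for an assessment of intervention effectiveness at the end of the study, when sample sizes will be smallest".

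The schedule is shorter in every place where it is described. Study Design and Rationale says "The longitudinal study will include assessments at baseline, 6m, 12m follow-up". Follow-up Visits says "Follow-up surveys will be conducted at 6 and 12 months after the intervention". The section on interim analysis and stopping rules places the interim look at the midpoint of follow-up, when nearly everyone has 6-month data, which fits a total of 12 months. No section schedules a 24-month visit.

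**The concern.** The power section is the only place that gives a time point for the final test of effectiveness, and nobody is scheduled to be assessed then. A reader cannot tell whether the efficacy comparison is meant for 12 months, or whether a 24-month visit was dropped from the design or left out of the procedures.

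Three things depend on the answer. The first is the retained sample and cohort size, which enter the design effect. The second is the horizon to which the tabulated differences in CES-D, injection risk and sex risk apply, because an intervention effect may differ between one and two years. The third is the choice of analysis time point: with two follow-up visits and three main outcomes, an unsettled time point leaves room to choose it after the data are seen.

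**Working it through.** **Inputs.** About 500 randomised, of whom 250 are injectors (Population). Two arms; equal allocation is assumed, giving 250 per arm and 125 injectors per arm. 25 cohorts per arm and 10% attrition per year (Power calculations). SDs of 4.5 for injection risk and 1.8 for sex risk (same section). For CES-D the section prints 8.3 as a variance; it is read here as an SD, which is an assumption.

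**Step 1: reproduce the stated sizes on two years.** Retained n = n₀ × 0.9².

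- Per arm: 250 × 0.81 = 202.5 (stated 200; simple subtraction, 250 × 0.80, gives exactly 200).
- Injectors per arm: 125 × 0.81 = 101.25 (stated 100).
- Per cohort: 202.5 / 25 = 8.1 (stated about 8).

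All three match, so the two-year horizon is not a stray phrase. The sizes rest on it.

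**Step 2: the same on one year.** Retained n = n₀ × 0.9.

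- Per arm: 250 × 0.90 = 225.
- Injectors per arm: 125 × 0.90 = 112.5.
- Per cohort: 225 / 25 = 9.

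None of these matches the stated figures. Against the stated 200, the gain is 225 / 200 = 1.125, or about 12%.

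**Step 3: the effect of the time point alone on power.** Use a two-sided 0.05 t-test on cohorts with K = 25 per arm and 2(K − 1) = 48 degrees of freedom. The standard error is √{2 × SD² × [1 + (m − 1) × ICC] / (K × m)}. Only m changes: 8 to 9, or 4 to 4.5 for injectors.

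For CES-D 2.0 at ICC 0:

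- m = 8: SE = √(2 × 8.3² / 200) = 0.83, and 2.0 / 0.83 = 2.41, giving power 0.66.
- m = 9: SE = √(2 × 8.3² / 225) = 0.783, and 2.0 / 0.783 = 2.56, giving power 0.71.

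| Outcome, difference | Two-year sizes, ICC 0 / 0.02 / 0.05 | One-year sizes, ICC 0 / 0.02 / 0.05 |
| --- | --- | --- |
| CES-D, 2.0 | 0.66 / 0.60 / 0.53 | 0.71 / 0.64 / 0.56 |
| Sex risk, 0.50 | 0.78 / 0.72 / 0.65 | 0.82 / 0.76 / 0.68 |
| Injection risk, 1.5 | 0.64 / 0.61 / 0.58 | 0.69 / 0.66 / 0.62 |

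Moving to 12 months raises power by about 3 to 5 points in each row.

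**Step 4: separate the other discrepancy.** The printed CES-D row for 2.0 is 0.92 / 0.88 / 0.83. With m = 8 and SD 8.3, the same formula gives 0.92 / 0.885 / 0.83 when K is 50 per arm, although the text gives 25 per arm. The gap between the printed row and either column above therefore comes from the cohort count, not from the follow-up horizon.

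**The case against.** The strongest reply is that the mismatch does little harm. The protocol says its power refers to the end of the study, and an end-of-study comparison exists at 12 months. Planning for two years of loss leaves more participants at 12 months than assumed, and the power section itself notes that earlier comparisons would have more power than it tabulates. This stands. The mismatch is conservative for N, and it does not threaten the feasibility of the trial.

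A reader might go further the other way and infer that the planned primary comparison does not exist, or that a two-year durability conclusion has been lost. The documents support neither. The protocol names main outcomes of interest but labels no comparison or time point as primary, and the Aims set no two-year durability objective. Only the two-year comparison lacks data.

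A reader might also set 0.71 / 0.64 / 0.56 beside the printed 0.92 / 0.88 / 0.83 and blame the time point for the fall. Step 4 shows that this is a separate matter.

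The reply does not remove the contradiction. The stated sizes, attrition and completers per cohort belong to a horizon that the schedule does not have. Nor does a larger retained N settle whether the assumed differences were meant for 12 or for 24 months.

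**Conclusion.** The point holds as an inconsistency between the power section and the visit schedule, of moderate severity. The stated 200 per arm, 100 injectors per arm and 8 per cohort are two-year figures; the scheduled design would retain about 225, 112 and 9. Taken alone, the correction adds about 12% to the retained sample and about 3 to 5 points of power.

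This rests on equal allocation of 500, attrition of 10% per year that is even across arms and cohorts, 25 cohorts per arm, unchanged differences and SDs, and 8.3 read as an SD. If 8.3 is taken literally as a variance (SD about 2.88), CES-D power for 2.0 points is about 1.00 and the time point makes no practical difference to it; the contradiction in the time point remains. Three sections point to 12 months, but the protocol does not say which text is out of date.

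**What to change.** Reconcile the Power calculations section with Study Design and Rationale, Follow-up Visits and the interim-analysis section. If the 12-month schedule stands:

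- name the 12-month assessment as the end-of-study efficacy time point;
- replace the two-year attrition with one year at 10%, giving about 225 per arm, 112 injectors per arm and 9 per cohort;
- confirm that the assumed differences in CES-D, injection risk and sex risk apply at 12 months;
- re-run the power tables on that basis, dealing with the cohort count as its own item.

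In that case the cost is protocol wording and a power re-run, with no added visits or participants. If a two-year assessment is intended, it has to be added to the schedule, and the cost is that of the extra follow-up.
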